**Table 2: Dietary intervention strategies**

|  | **Arm B: Low-carbohydrate/high monounsaturated diet** | **Arm A (control, AHA recommendation): high-carbohydrate/ low-saturated**  **fat diet** |
| --- | --- | --- |
| Energy | Non-restricted | Restricted |
| Total fat | Liberal, expected: >40% | < 35% |
| Saturated fat | not specifically restricted | < 7-10% |
| Dietary cholesterol | not specifically restricted | < 300 mg |
| Trans fats | not recommended | not recommended |
| Carbohydrates | Restricted: < 40gr in the first 2 months (induction phase), then gradually increasing to a maximum of 80 grams to maintain achieved weight loss,  expected: <35% | Not restricted, whole grains are recommended, expected: >55% |
| Specific foods added | 45 gr virgin olive oil/day ( expected at least 20% monounsaturated fat)  25 gr/day nuts  2 fish /wk |  |

### 4.2.1 Primary Endpoint

Changes in body fat compestion (mainly VAT) following the intervention

### 4.2.2 Secondary Endpoints

Changes in abdominal subcutaneous and hepatic fat following the intervention

### 4.2.3 Exploratory Endpoints

# 5 STUDY ENROLLMENT AND WITHDRAWAL

## 5.1 Participant Inclusion Criteria

In order to be eligible to participate in this study, an individual must meet all of the following criteria:

• Either abdominal obesity [waist circumference >102cm (40 inches) for men and >88cm (35 inches) for women], or serum triglycerides (TG)>150mg/dL and high-density-lipoprotein cholesterol (HDL‑c) <40mg/dL for men and <50mg/dL for women.
• Provision of signed and dated informed consent form
• Stated willingness to comply with all study procedures and availability for the duration of the
study.

## 5.2 Participant Exclusion Criteria

An individual who meets any of the following criteria will be excluded from participation in this study:

• Serum creatinine≥2mg/dl

• Impaired liver function (≥3 fold the upper level of ALT and AST enzymes)

• Active cancer

• Pregnancy or lactation

• Being highly physically active (more than 3 hours/week) or inability to take part in PA

• Participation in another trial.

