# PROTOCOL SUMMARY

| **Title:** | **Differential effect of weight-loss diet strategies on dynamics of abdominal and other fat depots and metabolic risk – the CENTRAL study: intervention trial** |
| --- | --- |
| **Précis:** | **Methods**: an estimate of 250 participants who have either a. central obesity or b. lean participants with poor dietary habits combined with hyper TG will be randomized by median VAT to the following groups: **Group 1:** low-fat diet. **Group 2 :** Low-carb /Mediterranean high MUFA and PUFA diet diet. Specific food items will be provided. After 6 months of intervention, the diet groups 1 and 2 will be re-randomized to continue with diet only or with combination of 4 hours/week aerobic and resistance gym exercise for the subsequent year, divided by 4 equal size groups of **Group A** (low-fat diet only), **Group A+** (low-fat diet +physical activity) , **Group B** (Low-carb/ high MUFA & PUFA diet only) and **Group B+** (Low-carb/ high MUFA & PUFA diet + physical activity). All groups will be guided for their dietary intervention by nutritional sessions. All the participants will be followed by 1.5-Tesla MRI imaging of fat and muscle, blood and urine biomarkers, clinical measurements (weight, waist circumference, blood pressure, energy expenditure) and electronic questionnaire of dietary, lifestyle and medical information. Furthermore, genetic tests will be performed following a genetic ethical committee approval. |
| **Objectives:** | To assess whether distinct lifestyle strategies can differentially affect specific body adipose pools.  ***Objective 1:***  To compare the effects of: low-carb/high-MUFA; and the currently recommended diet by the American Heart Association (low-fat diet) on the dynamics of body fat compesition (mainly VAT) during weight loss and regain-plateau phases by MRI with and without physical activity. ***Objective 2:***  To assess the effect of Low-carb/MED and Low- fat diets with or without PA on the dynamics of abdominal suncotenius intra-hepatic fat among participants with abdominal obesity or dyslipidemia. |
| **Endpoint** | Primary Endpoint: Body fat composition (changes in VAT). Important Secondary Endpoints: changes in abdominal subcutaneous fat sub-depots and hepatic fat. |
| **Population:** | Healthy adults with abdominal obesity/dyslipidemia. |
| **Phase:** | Phase 3 |
| **Number of Sites enrolling participants:** | Nuclear Research Center-Negev, Dimona, Israel  250 participants |

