The second randomization will be performed after six months of the dietary intervention. The dietary groups will be further divided into PA (A+, B+) and non-PA (A-, B-) groups. The participants assigned to PA groups will get 12 months free supervise gym membership. The PA intervention will be mostly aerobic exercise training (80%) and resistance training three times a week, for 30 minutes in the first month, 50 minutes in the second to fifth months, and 80 minutes for months six to twelfth. The PA participants will be guided first in the gym with the support of the professional sport trainers. We will follow the PA participants online by electronic gym card recording their frequency of access and duration to the sport center and will call them frequently to encourage adherence.

***Intervention:*  Arm A:** the 2006 currently recommended diet by the American Heart Association (AHA) ^35^ (Low-fat) calorie restricted diet, a more revised statement since the AHA 2000; **Arm B:** guidelines^40^Low-carb/MED non-calorie restricted diet (n=125). Based on our preliminary results, low-carb and Mediterranean diets each showed beneficial effects on several biomarkers. Thus, here we suggest to utilize an optimized diet strategy which combines the beneficial components of low carb (low-carb) and Mediterranean (high monounsaturated) diets (**Table 2**). For both arms moderate physical activity will be equally introduced and monitored. The participants will be guided to exercise 150 min/week of moderate intensity, primarily in the form of initiating walking. This will be monitored by podometers that will be provided. The advantage of this strategy is that the podometer reflects both exercise thermogenesis (walking) as well as components of Non-exercise activity thermogensis (NEAT)^41^. The format and quality of the sessions will be kept constant to ensure equal treatment intensity, except for the specific instructions and paper material distributed for each diet strategy.

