## 5.3 Strategies for Recruitment and Retention

Participants’ recruitment

The recruitment will be conducted among employees of the Nuclear Research Center, Dimona, Israel. The trial will be announced in the workplace and the potential participants will be contacted by the on-site clinic staff. The suitability of this setting is proven in several studies characterized by tight follow-up and/or interventions, which we performed in recent years^22^. Its advantages include an integral medical center, the possibility to perform most procedures within the workplace, and a secluded set of cafeterias amenable to dietary intervention.

Monitoring and Motivating Adherence

Adherence to the diet will be assessed by monitoring attendance of the nutritional sessions, and will be quantified via a self-administered validated electronic 127 item food-frequency questionnaires (FFQ) at baseline and after 6 and 18 months of intervention. By using electronic questionnaires, the completeness of the data was ensured by prompting the participants when a question was not answered or when an answer was not within a logical range. Adherence to the exercise intervention will be monitored frequently during the monthly group meetings and also quantified by calculating the METs/week using an electronic self-reported validated physical activity questionnaires at baseline and after 6 and 18 months. To motivate compliance, participants will be given a detailed individual report summarizing all their measurements after the completion of the trial. Participants who will not attend nutritional sessions or will decrease their gym attendance, as tracked online by the electronic gym entry monitor, will be contacted by telephone. Text messages will be sent to update participants and to motivate adherence to the diets on specific occasions (such as before and after holidays). Symptoms, adverse effects, quality of life, and medication usage will be measured at baseline and after 6 and 18 month, using validated electronic questionnaires^37, 42, 43^.

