**Physical Activity Intervention**

Starting after the first 6 months of dietary intervention, participants who will be randomized to added PA will receive a free supervised gym membership for the following 12 months. The intervention will include monthly 60-minute educational workshops, and training group sessions at the gym, directed by a certified fitness instructor, who will be blinded to the assigned diets of the participants. The exercise program will include three sessions/week of mostly aerobic training. In the first month participants will start with low intensity of aerobic training at 65% maximum heart rate for 20 minutes and 10 minutes of resistance training. Exercise will gradually increase to 45 minutes of aerobic training at 80% of maximum heart rate and 15 minutes of resistance training. The resistance training will be increased from one set of weights with 60% of the maximum weight up to two sets with 80% of the maximum weight and will include: leg extension, leg curl, elbow flexion, triceps extension, lateral pull-down, lower back extension and bent leg sit-ups.

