## 10.6 Measures to Minimize Bias

### 10.6.1 Enrollment/ Randomization/ Masking Procedures

Participants will be randomly assigned to one of two equal-caloric diets for the entire study period: a low-fat diet (n=125) or a Mediterranean/low-carbohydrate diet (n=125). After 6 months of dietary intervention, each diet group will be further randomized into added PA groups (LF^PA+^, MED/LC^PA+^) or no added PA groups (LF^PA–^, MED/LC^PA–^) for the last 12 months of intervention. The randomization will be performed with an allocation ratio of 1:1 to the two treatment groups, within strata of baseline VAT area for the first randomization, and of address of residence (to ensure similar geographical distance from the gym) in the second randomization (in blocks of two). Participants will be randomized after all had been recruited, in one phase, after their strata characteristics will be defined.

The participants, who will be randomized in the same time point, will be aware of the intervention to which they will be assigned (open-label). Study investigators will be blinded to the intervention group identities.

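### People already exercising for much of the prescribed gym time are eligible, yet the fixed covariate list omits the METs/week the trial collects, and the gym dose is stated inconsistently

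*Protocol*

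**What the plan says.** **Entry.** Section 5.2 excludes anyone "Being highly physically active (more than 3 hours/week) or inability to take part in PA". Exactly three hours a week, or less, is eligible. The type and intensity of activity are not specified.

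**Gym programme.** The protocol describes it in three places.
- Section 6.1: "The exercise program will include three sessions/week of mostly aerobic training". Sessions start at 20 minutes aerobic plus 10 minutes resistance, and then "Exercise will gradually increase to 45 minutes of aerobic training at 80% of maximum heart rate and 15 minutes of resistance training".
- Section 4.1: three sessions a week of 30 minutes in the first month, then "50 minutes in the second to fifth months, and 80 minutes for months six to twelfth".
- Protocol Summary: "combination of 4 hours/week aerobic and resistance gym exercise for the subsequent year".

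**Background activity.** Section 4.1 also says, for both diet arms, "The participants will be guided to exercise 150 min/week of moderate intensity, primarily in the form of initiating walking".

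**Second randomisation.** After six months, "each diet group will be further randomized into added PA groups" or no added PA (section 10.6.1), stratified by address of residence.

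**Measurement and models.** Section 5.3 says adherence to exercise is "quantified by calculating the METs/week using an electronic self-reported validated physical activity questionnaires at baseline and after 6 and 18 months". Section 10.4.1 lists the adjustment variables for all models: age, sex, abdominal obesity at entry, and weight change over the 18 months. Physical activity is not among them.

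**The concern.** The PA factor is one half of the 2×2 design, and its main endpoint is change in visceral fat. If some participants already exercise for as long each week as the programme asks, two questions arise. One is whether the PA+ and PA– groups will differ in activity as much as the prescription suggests. The other is whether variation in prior activity adds noise or chance imbalance to the comparison.

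The protocol collects a measure of prior activity but does not use it in either the second randomisation or the models. Because section 10.4.1 states its list for all models, the omission is a stated choice and not a detail left open.

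**Working it through.** **Step 1: weekly gym time against the ceiling.** The ceiling is 3 × 60 = 180 minutes a week. I read the session lengths in section 4.1 as minutes per session.

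| Source | Weekly minutes | 180 as a share |
|---|---|---|
| Section 6.1, start | 3 × (20 + 10) = 90 | 200% |
| Section 6.1, maximum | 3 × (45 + 15) = 180 | 100% |
| Section 4.1, gym month 1 | 3 × 30 = 90 | 200% |
| Section 4.1, gym months 2–5 | 3 × 50 = 150 | 120% |
| Section 4.1, gym months 6–12 | 3 × 80 = 240 | 75% |
| Section 4.1, 12-month mean | (1 × 90 + 4 × 150 + 7 × 240)/12 = 2370/12 = 197.5 | 91% |
| Protocol Summary | 4 × 60 = 240 | 75% |

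The three sources do not agree. Section 6.1 peaks at 180 minutes, section 4.1 builds up to 240, and the Summary gives 240 for the whole year. Equality with the ceiling holds for the section 6.1 maximum only. On every version, though, someone at the ceiling already exercises for at least 75% of the prescribed weekly time.

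**Step 2: does this change the randomised contrast?** Let h be usual activity, g the gym time attended, and s the usual activity dropped in exchange for gym sessions.
- Mean total in PA–: h
- Mean total in PA+: h + g − s
- Difference: g − s

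Randomisation makes the mean of h equal in expectation, so h cancels. A high h matters for achieved minutes only through s. For one person at the ceiling:
- At the section 6.1 maximum (g = 180), the difference runs from 180 minutes (no substitution) to 180 − 180 = 0 (full substitution).
- At the 240-minute dose, it runs from 240 to 240 − 180 = 60.

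The protocol gives neither the share of participants near the ceiling nor the extent of substitution. It also does not say whether added exercise removes less visceral fat in people already active. No trial-level size can therefore be computed.

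**Step 3: which activity measure may enter which model?**
- *Baseline METs/week* precede both randomisations, so they are a valid covariate for the diet, PA and diet-by-PA terms.
- *Month-6 METs/week* follow six months of diet. Diet may have altered them, so adjusting the diet or interaction terms for them could remove part of a diet effect. They suit only the PA comparison within a diet group, and only if recorded before the second randomisation. Section 7.1.1 states that order for the month-6 waist measurement. The protocol does not state it for the questionnaire.

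**The case against.** A three-hour cut-off is a defensible eligibility choice, and the protocol does not say what the criterion is for. Equal minutes are not an equal programme: section 6.1 describes supervised training that rises to 80% of maximum heart rate, with structured resistance work. A reader might infer that people already doing the whole programme are being enrolled as controls, or that the PA contrast is therefore narrowed. The documents support neither. The criterion concerns time alone, and the comparison is of added activity, for which usual activity balances in expectation. A percentage loss of contrast could be produced by assuming a share of active participants and full substitution, but it would describe those assumptions and not this trial.

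Section 4.1 also guides both diet arms to 150 minutes a week, which equals its own gym prescription for months 2–5. That may shape activity in the PA– group more than the entry ceiling does. Achieved activity is already tracked by questionnaire, gym card and session attendance. A covariate cannot restore exposure lost to substitution.

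All of this stands. It removes the case for changing the ceiling and for claiming bias or a known dilution. It does not answer the narrower point that a relevant pre-randomisation measure is collected and then excluded from every model by a fixed list. The 150-minute guidance is a further reason to expect activity to vary within both PA groups.

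**Conclusion.** The point holds in a limited form and is minor.
- People already exercising for much of the prescribed weekly time are eligible. The ceiling is 100% of the maximum in section 6.1 and 75% of the 240 minutes in section 4.1 (months 6–12) and the Summary.
- The dose statements in the Summary, section 4.1 and section 6.1 contradict each other and must be reconciled.
- The added-PA contrast is not biased. It may be narrowed only through substitution or a weaker response in active people, and the size of either is unknown.
- Leaving prior activity out of all models forgoes precision and protection against chance imbalance that the trial's own data could supply. The gain depends on how strongly baseline METs/week, a self-reported measure, predict change in visceral fat. The protocol does not give that correlation.

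**What to change.** 1. In section 10.4.1, add baseline METs/week as a covariate in the 2×2 diet-by-PA models of fat-depot change.
2. Restrict any use of month-6 METs/week to the PA comparison within diet group, and state that the questionnaire must be completed before the second randomisation.
3. Report the PA+ versus PA– difference in METs/week change from month 6 to month 18 as the achieved contrast, so that a null PA result can be interpreted.
4. Reconcile the weekly gym time across the Protocol Summary, section 4.1 and section 6.1. Which figure applies is for the investigators to decide.

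No change to the entry ceiling is proposed. The cost is one degree of freedom and revised wording, with no new data collection.

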## 5.3 Strategies for Recruitment and Retention

Participants’ recruitment

The recruitment will be conducted among employees of the Nuclear Research Center, Dimona, Israel. The trial will be announced in the workplace and the potential participants will be contacted by the on-site clinic staff. The suitability of this setting is proven in several studies characterized by tight follow-up and/or interventions, which we performed in recent years^22^. Its advantages include an integral medical center, the possibility to perform most procedures within the workplace, and a secluded set of cafeterias amenable to dietary intervention.

Monitoring and Motivating Adherence

Adherence to the diet will be assessed by monitoring attendance of the nutritional sessions, and will be quantified via a self-administered validated electronic 127 item food-frequency questionnaires (FFQ) at baseline and after 6 and 18 months of intervention. By using electronic questionnaires, the completeness of the data was ensured by prompting the participants when a question was not answered or when an answer was not within a logical range. Adherence to the exercise intervention will be monitored frequently during the monthly group meetings and also quantified by calculating the METs/week using an electronic self-reported validated physical activity questionnaires at baseline and after 6 and 18 months. To motivate compliance, participants will be given a detailed individual report summarizing all their measurements after the completion of the trial. Participants who will not attend nutritional sessions or will decrease their gym attendance, as tracked online by the electronic gym entry monitor, will be contacted by telephone. Text messages will be sent to update participants and to motivate adherence to the diets on specific occasions (such as before and after holidays). Symptoms, adverse effects, quality of life, and medication usage will be measured at baseline and after 6 and 18 month, using validated electronic questionnaires^37, 42, 43^.

## 5.4 Participant Withdrawal or termination

5.4.1 Reasons for Withdrawal or Termination

Participants are free to withdraw from participation in the study at any time upon request.
An investigator may terminate participation in the study if any clinical adverse event (AE), laboratory abnormality, or other medical condition or situation occurs such that continued participation in the study would not be in the best interest of the participant

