5.4.2 Handling of Participant Withdrawals or termination

The participants who withdraw or discontinue early will not be replaced.

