## 6.2 Study agent Accountability Procedures

# 7 STUDY PROCEDURES AND SCHEDULE

## 7.1 Study Procedures/Evaluations

### 7.1.1 Study specific procedures

**Magnetic Resonance Imaging (MRI)**

To assess body fat depots/deposits, we will perform a 45-minute 1.5-Tesla MRI (Ingenia 3.0 T, Philips Healthcare, Best, the Netherlands) scans at baseline and after 18 months. In a sub-set of, randomly selected, 50% of the participants, we will perform MRI measurement after 6 months of intervention. The scanner utilize a 3D modified DIXON (mDIXON) imaging technique without gaps (2mm thickness and 2mm of spacing), fast-low-angle shot (FLASH) sequence with a multi-echo two-excitation pulse sequence for phase-sensitive encoding of fat and water signals (TR,3.6ms; TE1,1.19ms; TE2,2.3ms; FOV 520×440×80mm; 2×1.4×1mm voxel size). Four images of the phantoms will be generated, including in-phase, out-phase, fat and water phase. A breath-hold technique will be used to avoid motion artifacts when the chest and abdomen will be scanned. In all simultaneous fat depots quantifications and comparisons, observers will be blinded to time point and group treatment. All fat depots will be assessed by one or two raters. To validate our mDIXON quantification of fat ratio, we will test five tubes filled with 0%, 25%, 50%, 75% and 100% of oil to observe a linear relation.

***Abdominal fat depots:*** We will quantify abdominal fat using the MATLAB-based semi-automatic software. We will calculate mean VAT and SAT from three axial slices: L5-S1, L4-L5 and L2-L3. Quantification of the fat mass regions will include the area of each fat type and its proportion (percentage) of the total area of all fat types.

***Hepatic fat content:*** We will quantify the percentage of hepatic fat using PRIDE software from Philips Medical Systems. We will calculate mean percentage from four 2D slices (3cm intervals divided into quarters) by utilizing the region of interest (ROI) approach, which is based on measurements of tissue densities (fat/fat+water) using the Fat Ratio Calculation.

***Resting metabolic Rate (RMR)*** We will mesure RMR by indirect calorimetry (QUARK REE by COSMED, Rome, Italy) in which the quantity of oxygen consumed and carbon dioxide produced are measured and converted into kcal using the Weir equation.

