### 7.3.5 Early Termination Visit

NA

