### 8.4.4 Events of Special Interest

### 8.4.5 Reporting of Pregnancy

Women participants will be required to report their pregnancy to [name], MD, Nuclear Research Center-Negev (the head of the integral medical center in the workplace) and the intervention will be discontinued.

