## 10.3 Analysis Datasets

We will check the assumptions for all the statistical analyses to ensure that none were violated. We will perform intention-to-treat analyses, including all the participants, by imputing the missing observations for adipose tissues for the individuals with missing data at 18-months by the multiple imputation technique, with the following predictors: age, gender, baseline weight/ BMI and waist circumference at the end of the intervntion. For missing data of body weight, we will use the last observation carried forward.

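### Stopping the intervention is not separated from leaving the study, and no month-18 MRI is planned after termination, so those participants' primary outcome goes uncollected

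*Protocol*

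**What the plan says.** - **Termination (Protocol 5.4.1).** "An investigator may terminate participation in the study if any clinical adverse event (AE), laboratory abnormality, or other medical condition or situation occurs", qualified by "such that continued participation in the study would not be in the best interest of the participant". The decision is discretionary, and what it ends is participation in the study. The same section lets participants withdraw on request.
- **Handling afterwards (5.4.2).** "The participants who withdraw or discontinue early will not be replaced". Nothing is said about further outcome measurement.
- **Exit visit.** The section headed "7.3.5 Early Termination Visit" contains only NA.
- **Pregnancy (8.4.5).** Here "the intervention will be discontinued"; whether follow-up goes on is not stated.
- **MRI (7.1.1).** Scans are planned for everyone at baseline and month 18. For month 6: "In a sub-set of, randomly selected, 50% of the participants, we will perform MRI measurement after 6 months of intervention". Table 3 marks a month-6 MRI without that limit.
- **Analysis (10.3).** "We will perform intention-to-treat analyses, including all the participants", with missing 18-month adipose data filled by multiple imputation. The listed predictors are age, sex, baseline weight or BMI, and waist at the end of the intervention. Missing body weight is carried forward.
- **Sample size (10.5).** 250 participants for a VAT difference of 3.57 cm², 5% alpha and 80% power. No SD and no allowance for dropout is given.

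**The concern.** An intention-to-treat analysis of VAT needs the month-18 scan from people who stopped their assigned programme as well as from those who kept to it. Many who stop could still be scanned. The protocol has one exit route for medical reasons, it removes the person from the study, and no measurement is planned after it. Whether a scan is done is a matter of trial conduct, so no analysis plan written later can recover one that was never made.

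Precision and the meaning of the primary comparison are both at stake. People who stop for a medical reason may change differently from those who continue, and values imputed from those who continue need not resemble what a scan off the intervention would have shown.

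**Working it through.** **1. What exists for a participant terminated before month 18**

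| Item | Planned (7.1.1, clinical measurements, Table 3) | Left before month 6 | Left between months 6 and 18 |
|---|---|---|---|
| VAT by MRI | 0 and 18; month 6 in a random half (7.1.1) or for all (Table 3) | baseline only | baseline, plus month 6 for about half (7.1.1) or all (Table 3) |
| Waist | 0, 6, 18 | baseline only | baseline and month 6 |
| Weight | monthly | last value, carried forward | last value, carried forward |

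On either reading of the month-6 schedule there is no 18-month VAT. The adverse event follow-up in 8.3 runs to resolution, but it is safety follow-up and includes no MRI.

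**2. What the imputation in 10.3 can use for these people**

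Of the four listed predictors, waist at the end of the intervention would normally be missing. Reading it as the participant's own last day on the intervention does not help, because no visit is planned then. That leaves age, sex and baseline weight or BMI, all baseline values. Arm, baseline VAT, month-6 VAT and the reason for stopping are not listed. If arm is left out, the imputed values carry no treatment difference beyond what the listed predictors convey.

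**3. The plan's own figure**

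Without an SD, N = 250 cannot be reproduced from the stated inputs. Solving backwards for 125 per diet group, two-sided alpha 0.05 and 80% power:

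- standardised difference = (1.960 + 0.842) × √(2/125) = 2.802 × 0.1265 = 0.354
- implied SD = 3.57 / 0.354 ≈ 10.07 cm²

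As a check, an SD of 10 cm² gives 124 per group, 248 in all. The SD is back-solved and has no source in the protocol. With an SD of 8 or 12 cm², 250 participants would give 94% or 65% power.

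**4. Illustration of lost precision**

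Let m be the fraction of final VAT values missing, equal in both groups. If full data give 80% power, the SD cancels:

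power = Φ(2.802 × √(1 − m) − 1.960)

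| m (assumed) | values left | power | N to restore 80% (250 / (1 − m), rounded up) |
|---|---|---|---|
| 0 | 250 | 80.0% | 250 |
| 5% | 237.5 | 78.0% | 264 |
| 10% | 225 | 75.7% | 278 |
| 15% | 212.5 | 73.3% | 295 |

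This treats a missing value as contributing nothing. That is an approximation to multiple imputation, reasonable when only weak baseline predictors remain.

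**5. Bias**

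If those lost differ from those retained by the same amount g in both arms, a comparison of observed values is off by (m₁ − m₂) × g. This is zero when loss is equal and changes sign with the direction of the imbalance. The protocol gives neither m₁ and m₂ nor g, so no figure can be derived from it.

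**The case against.** The strongest reply is that the rule is narrow. It is discretionary and applies only when continuing is against the participant's interest. Section 5.3 has people who miss sessions or cut gym attendance telephoned, not removed. Section 2.3.1 expects no risk, and 5.2 excludes people unable to take part in physical activity. Everyone stays in the analysis through imputation. All of this stands: it limits how often the gap opens, but it does not supply a scan when it does.

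Four stronger readings are tempting, and the documents do not support them.

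- A reader might infer that any adverse event or laboratory abnormality ends participation. The best-interest condition rules that out.
- A reader might infer that observed outcomes are discarded. They are never collected, and 10.3 then imputes them.
- A reader might take 8.4.5 as proof of a second status, off the intervention but still followed, that contradicts 5.4.1. Section 8.4.5 is silent on follow-up. The two sections use different terms and need reconciling, but they do not conflict outright.
- A reader might infer that loss is likely to differ by arm and to bias the result. Only half the participants get the gym programme, so a difference is possible. A 5 to 10 point imbalance with a 10 cm² gap would give 0.5 to 1.0 cm², or 14% to 28% of 3.57 cm². Both inputs are invented, though, and the formula describes a completer analysis that the protocol does not plan. The 85% two-year adherence in section 2.1 comes from an earlier trial, is not split by arm, and is not a rate of investigator termination.

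**Conclusion.** The gap in outcome collection is real. As written, anyone terminated before month 18 has no final VAT, and the intention-to-treat result for that person rests on an imputation model with little information about them. How often this happens is not stated, and neither the size nor the direction of any bias can be derived from the protocol. The power figures, about 78% to 73% for a 5% to 15% loss, rest on assumed loss rates and on full data giving the planned 80%. They cover loss from any cause, so they overstate what investigator terminations alone would do if other withdrawals make up part of it. This is an inexpensive improvement to protect the primary endpoint; it does not show that the planned comparison is invalid.

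**What to change.** 1. Leave the investigator's safety decision in 5.4.1 as it is, and reconcile the wording of 5.4.1 and 8.4.5 so that each says whether it refers to the intervention or to study participation. What an adverse event or a pregnancy should lead to clinically is for the sponsor and investigators to settle.
2. Record stopping the intervention separately from leaving the study or withdrawing consent, with date and reason.
3. Replace NA in 7.3.5 with a request that everyone who has not withdrawn consent to follow-up still attend the month-18 MRI, waist, weight and blood measurements, unless the measurement itself is contraindicated.
4. State in 10.3 that these values enter the intention-to-treat analysis. For those who still lack a scan, naming arm and baseline VAT (and month-6 VAT where available) as imputation predictors would help.

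The cost is a short amendment with matching consent wording, and some effort to bring people back. No new procedure is needed, since the month-18 scan is already scheduled for everyone and the participants work at one site with an on-site clinic. Values measured off the intervention may make the estimated effect slightly smaller. People who refuse follow-up will still be missing.
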